**4. Post-intervention phase**

End line assessment of maternal knowledge of infant feeding and infant feeding practices, 24 hour dietary recall (consuming foods from 4 or more food groups, recommended number of meals and snacks per day) will be done by using the same pretested semi-structured questionnaire as was used in baseline assessment in study and control area (Annexure 2). The status of undernutrition will be assessed by anthropometry of the infant (wt/age, wt/length, length/age). Similarly, the knowledge of ANMs and *anganwadi* workers on infant feeding and status of growth monitoring will be checked by the same pretested semi-structured questionnaire (Annexure 3) in both intervention and control arm.

**Study Tools**

1. Focus group discussion will be conducted with mothers/ANMs/AWWs/Community representatives to explore the culturally appropriate foods, gap between knowledge and action of mothers, frequency of feeding etc using focus group discussion guide (Annexure 1).
2. Pretested semi-structured questionnaire will be administered to the mothers (Annexure 2) participating in the study to assess their baseline and post-intervention knowledge of infant feeding, infant feeding practices e.g. number of meals and snacks consumed per day and hand hygiene practices. 24 hour dietary recall form will be used to assess the infant feeding. The proportion of children consuming recommended number of semi-solid/soft meals and snacks per day according to WHO will be determined at baseline and 6 months in intervention and control groups. The infant’s age will be recorded from the mother and child health card or birth certificate.
3. Pretested semi-structured questionnaire will be administered to the ANMs/AWWs (Annexure 3) participating in the study to assess their baseline and post-intervention knowledge of infant feeding practices and advices given to mothers/ caregivers.
4. Separate training modules will be designed for mothers (Annexure 5) and health workers (Annexure 4). The content of mother’s training module is consistent with age specific feeding recommendations made by World Health Organization, 2001 and Complementary Feeding Counseling: a training course made by World Health Organization, 2004 [61,62]. The content of ANMs and AWWs training module is consistent with Complementary Feeding Counseling: a training course made by World Health Organization, 2004 [62].
5. Anthropometric measurements will be done by standardized weighing scale (Digital Salter Model 235, CMS weighing equipment) and stadiometer (SECA height board UNICEF) [59,60]. The nutritional status of the children will be assessed by plotting the weight and height of the children on World Health Organization (WHO) 2006 Growth Standards growth charts using z-scores. Children falling below the −2 standard deviation (SD) cut-off would be considered as underweight (weight for age), stunted (height for age), and wasted (weight for height).

**Data Collection**

Data on anthropometry will be collected at baseline and 6 months of intervention in both study and control group. Data collection will be done by the chief investigator who is a junior resident in the Department of Community Medicine. After data collection, all filled forms will be manually checked for completeness and consistency.

**Outcome measures**

**Primary outcome**

- Mean change in the weight for age.

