The present study is planned with an aim to ascertain the effectiveness of a culturally appropriate nutritional education intervention delivered through health services to improve growth and complementary feeding of infants of age 6 to 12 months in Chandigarh; and to develop a child undernutrition tracking module for health workers to monitor child growth. The study design will be quasi-experimental. The study and control area will be selected purposively. The study will be conducted among vulnerable, migrant population usually belonging to lower/lower middle socioeconomic groups. The primary end point will be mean change in weight for age. The study population will be mother infant dyad with the age of infants between 4-6 months. Mother infant dyad will be enrolled at the baseline, and they will be followed up for 6 months after initiation of the intervention. Prior formative research in the form of focus group discussions will be conducted with mothers, health workers and community workers to explore culturally appropriate foods, affordability and knowledge regarding feeding practices. At the baseline, a pretested semi-structured questionnaire will be used to assess the knowledge and feeding practices of mothers and health workers. A baseline anthropometry of the infants will be done. During the intervention phase, both mothers and health workers will be trained as per modules of World Health Organization. The mothers will be provided nutritional education about culturally appropriate, easily available, and affordable low cost home based standard recipes that they will feed their children. The health workers will support mothers at individual level and do the growth monitoring of the children. A monthly work plan will be prepared for each health worker for monitoring growth of the infants. The resident will do supervision of health workers in the field every two months. At the end of the study, the same pretested semi-structured questionnaire and anthropometry will be used to find the improvement in feeding practices and growth respectively. The anthropometric data will be entered in excel sheet and z sores will be calculated. Statistical analysis will be done by using Statistical Package for Social Sciences version 16. Effectiveness of the intervention will be measured by calculating the difference in difference in mean change in weight between the intervention and control group.

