**Sample size:**

The sample size for the study is calculated by using the formula = (u+v)²*(σ₁²+σ₀²)/(µ₁-µ_0_)²

where

u=two sided percentage point of normal distribution corresponding to 100% - power=1.28

v=percentage point of normal distribution corresponding to (two sided) significance level=1.96, assuming 80% power with 95% C.I. [58].

(µ₁-µ₂)= difference between the means

d₁, d₀ = standard deviations

Difference between the mean weights is assumed to be 250 g [20].

Sample size thus calculated to be= [(1.28+1.96)²*((0.65)^2^+ (0.65)²]/ (0.25)² = 182. This is the minimum sample size of infants to be included in the study per arm.

Considering attrition rate of 10%, sample size per arm = 202.

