**Sampling Technique**

A list of all mother-infant dyads, where age of infants will be between 4 to 6 months, will be obtained from the *anganwadi* centers of the study and control area. Mother-infant dyads will be selected by simple random sampling in study and control groups from the complete list. Final inclusion will be done for those mother-infant dyads who will meet the study criteria. In the first month of enrolment, all mother-infants dyads between four to six months old infant will be enrolled. Enrollment will be continued thereafter till the required sample size is achieved in both study and control groups.

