**Statistical Analysis**

The data will be entered in Microsoft excel version 7. The data will be presented in frequencies, proportion and means. Statistical analysis will be done by using Statistical Package for Social Sciences version 16. T-test will be used to assess level of significance in difference between the means of the group. Chi square test will be done to assess significance of difference between proportions. Effectiveness will be measured by calculating the difference in difference in mean change in weight between the intervention and control group. Repeated measure ANOVA will be used to assess the difference in mean change in weight in the intervention group at baseline, 3 months and 6 months post intervention.

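### The declared primary outcome is change in weight for age, but effectiveness and sample size are set on weight in kg, which is open to confounding by enrolment age in this two-area design

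*Protocol*

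**What the plan says.** Two places name the outcome. The Primary outcome entry is "Mean change in the weight for age", and the Summary agrees: "The primary end point will be mean change in weight for age". Neither uses the word z-score. However, the Summary, the part on supervision of health workers and the Study Tools section all have z-scores calculated from the anthropometry, and Study Tools specifies the WHO 2006 standards.

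The analysis is written for another variable. Under Statistical Analysis: "Effectiveness will be measured by calculating the difference in difference in mean change in weight between the intervention and control group". The last sentence of the Summary says the same. The within-arm analysis is also on weight: "Repeated measure ANOVA will be used to assess the difference in mean change in weight in the intervention group". The between-group test is given as "T-test will be used to assess level of significance in difference between the means of the group", with no covariate named.

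The Sample size section uses weight too: "Difference between the mean weights is assumed to be 250 g". The SD is 0.65 per arm, in kg by implication because the difference is entered as 0.25.

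On design, each arm is one purposively selected area (Burail for the intervention, Maloya for control). Infants may enter at any age from 4 to 6 months. Under Sampling Technique, "In the first month of enrolment, all mother-infants dyads between four to six months old infant will be enrolled", and enrolment then continues until each arm reaches its target.

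**The concern.** A primary outcome and its primary analysis should concern the same variable. Here a reader can take the primary result to be a difference in kg or a difference in weight for age, and both have support in the text. If the two disagree, either can be presented as primary after the data are seen. An SAP cannot settle this without departing from one of the protocol's own statements.

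The choice matters more here than in a randomised trial. Six-month weight gain in infancy depends on the age at which the six months begin. Difference in difference removes a fixed gap in baseline weight between the areas. It does not remove a gap in expected gain that arises because one arm started younger. Weight for age is scaled for age and sex, and raw kg is not.

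**Working it through.** **1. The variable in each place**

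| Place | Variable |
|---|---|
| Primary outcome | change in weight for age |
| Summary, primary end point | change in weight for age |
| Summary, last sentence | difference in difference in change in weight |
| Statistical Analysis, effectiveness | difference in difference in change in weight |
| Statistical Analysis, repeated-measures ANOVA | change in weight |
| Sample size | difference in mean weights, 250 g, SD 0.65 |

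The Sample size section is one step further away, because it speaks of mean weights and not of change.

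**2. The stated sample size**

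The printed expression is (1.28 + 1.96)² × (0.65² + 0.65²) / 0.25² = 10.4976 × 0.845 / 0.0625 = 141.9, not the stated 182. That is a separate defect. Since 182 / 0.9 = 202.2, the planned 202 per arm does follow from 182, so 182 completers per arm is used below.

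**3. What 182 per arm detects on a z-score scale**

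At 80% power and two-sided 5%, the detectable difference is (1.96 + 0.84) × √(2/182) = 2.80 × 0.1048 = 0.29 SD. The documents give no SD for change in weight-for-age z-score. If it is 0.7 to 1.0 (assumption), this is 0.21 to 0.29 z. The planned standardised effect in kg is 0.25 / 0.65 = 0.385 SD, which is larger than 0.29 SD.

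**4. How enrolment could make entry ages differ**

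Inputs from Study design: 862 infants under 1 year in Burail and 483 in Maloya. Prorated to a 2-month age band:
- Burail: 862 × 2/12 = 143.7
- Maloya: 483 × 2/12 = 80.5

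Assume that all of these are listed, eligible and consenting, with mean age 5.0 months, and that the remaining places up to 202 go to infants who reach the age band later, at mean age *a*. Then mean age = [pool × 5.0 + (202 − pool) × *a*] / 202.

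| *a* (assumed) | Burail | Maloya | Gap (months) |
|---|---|---|---|
| 4.5 | 4.856 | 4.699 | 0.16 |
| 4.0 | 4.711 | 4.399 | 0.31 |

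Maloya, the control area, is younger in both cases.

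**5. From age gap to bias in kg**

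Assume six-month gain falls by 0.05 to 0.25 kg per month of later start. No such slope is in the documents.
- Gap 0.16: 0.156 × 0.05 = 0.008 kg, to 0.156 × 0.25 = 0.04 kg
- Gap 0.31: 0.313 × 0.05 = 0.016 kg, to 0.313 × 0.25 = 0.08 kg

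The overall range is about 0.01 to 0.08 kg. Younger controls would gain more, so the bias lowers the apparent benefit. For scale, the Bangladesh trial in the Review of Literature is reported with a six-month difference of 0.86 − 0.77 = 0.09 kg.

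**6. Sensitivity**

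The gap equals (5.0 − *a*) × (difference in pools) / 202. If half the infants in each area are eligible, it halves to 0.08-0.16 months. If 4 to 6 months is read as a 3-month band (mean 5.5, Burail pool capped at 202, Maloya 120.75), it rises to 0.40-0.60 months and the bias to 0.02-0.15 kg.

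**The case against.** Weight in the Statistical Analysis section may be shorthand for weight for age, since both terms appear in the Summary, and the Primary outcome entry never says z-score. The second part is correct: the z-score reading comes from other sections. The first does not rescue the text, because the Sample size section is plainly in grams and no reading of weight for age equals unadjusted kg.

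Covariates are commonly left to an SAP. This stands, and the absence of an age or sex term is not itself the finding. The finding is that the protocol fixes an analysis variable that differs from its declared outcome.

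The accrual pattern is inferred. Sampling Technique does not say that later entrants are only those newly reaching 4 months, and it also describes simple random sampling from the list. Residence, migration, illness and consent criteria will shrink the pools. All of this stands, which is why the bias is shown as a range under assumptions. The 4-6 month window also caps the possible gap.

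Moving to z-scores does not fully remove the dependence on entry age. The Introduction places the high malnutrition rate between 6 and 24 months, and infants enrolled at 4 and at 6 months spend different parts of follow-up in that window. This stands too, and is why the z-score analysis should also adjust for enrolment age.

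**Conclusion.** The mismatch is in the text and rests on no assumption: the outcome is change in weight for age, while the effectiveness measure and the sample size are in weight. It should be corrected before analysis.

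The confounding is a possibility. Its illustrative size of 0.01-0.08 kg rests on full eligibility of listed infants, the assumed later-entry ages and the assumed slope.

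A reader might infer more, and the documents do not support it:
- That the kg comparison is known to be confounded. No entry-age data exist yet, and the accrual pattern is not specified.
- That about a third of the 250 g target is at risk. The figure of 0.078 / 0.25 = 31% needs every later entrant at exactly 4.0 months together with the steepest assumed slope. A full one-month age gap would exceed the 0.31 months derived above more than threefold.
- That the bias could create a false benefit. Under this mechanism it runs against the intervention.
- That the arms will differ in sex. Nothing in the protocol points to such an imbalance.
- That the trial is underpowered for weight for age. No z-score target or SD is given, and 182 per arm detects a smaller standardised difference (0.29 SD) than the one planned in kg (0.385 SD).

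**What to change.** - **Summary and Statistical Analysis:** name one primary estimate that matches the Primary outcome entry. It should be the between-arm difference in change in weight-for-age z-score (WHO 2006 standards, by sex and exact age) from baseline to 6 months, adjusted for age at enrolment. Add the word z-score to the Primary outcome entry.
- **Kg gain:** keep it as a supportive analysis, adjusted for baseline age and sex.
- **Sample size:** state that the calculation is for weight in kg, and add the z-score difference detectable at the planned size: about 0.29 SD at 80% power with 182 per arm, or 0.21-0.29 z if the SD of change is 0.7-1.0 (to be labelled as an assumption).

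The cost is minor rewording and a little more analysis. Weight, date of birth or age, and sex are already collected, and z-scores are already to be calculated.

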**Secondary outcome:**

- Mean change in the weight for height.
- Mean change in the Height for age.
- Change in level of maternal knowledge and practice of recommended infant and child feeding practice following intervention.
- Change in proportion of infants who were consuming foods from four or more food groups
- Change in proportion of infants who were consuming the recommended number of meals and snacks per day

**Statistical Analysis**

The data will be entered in Microsoft excel version 7. The data will be presented in frequencies, proportion and means. Statistical analysis will be done by using Statistical Package for Social Sciences version 16. T-test will be used to assess level of significance in difference between the means of the group. Chi square test will be done to assess significance of difference between proportions. Effectiveness will be measured by calculating the difference in difference in mean change in weight between the intervention and control group. Repeated measure ANOVA will be used to assess the difference in mean change in weight in the intervention group at baseline, 3 months and 6 months post intervention.

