**Study design**

The study design will be quasi-experimental. The study and control area will be selected purposively. Study area will be Burail, an urbanized village in the catchment area of Civil Hospital, sector 45, Chandigarh. It is also one of the field practice area of department of Community Medicine, School of Public Health, PGIMER, Chandigarh. The population of Burail is 47,869 with 862 children below 1 year of age, as per annual health survey report, 2015-16. Most of the residents are migrants from neighboring states like UP, Bihar, Uttarakhand, Haryana and Himachal Pradesh, and belong to low or middle socio-economic groups. About 97% of children aged between 12 to 23 months in Burail are fully immunized, as per annual health survey report, 2015-16. Burail has 7 auxiliary nurse midwives (ANMs) and 19 anganwadi workers and centers. The control area will be Maloya, another urbanized village in Chandigarh. The background characteristics of control area are similar to study area in terms of vulnerability, migration of population, geographical location, socioeconomic status and baseline child health status. It has a population of 28,176 with 483children below 1 year of age as per annual health survey report 2015-16 of Civil Dispensary, Maloya. Maloya has 3 ANMs, 1 ASHA, 26 *anganwadi* workers and centers. About 90% of children aged 12-23 months are fully immunized in this area as per annual health survey 2015-16.

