**3. Intervention Phase**

***a. Intervention for mothers/ caregivers:***

The intervention will be delivered in community settings at mother-infant dyad level. The intervention duration will be six months. Mothers/caregivers will be provided nutritional education as per the modules.

**Module for mothers**: The content is consistent with age specific feeding recommendations made by World Health Organization, 2001 [61]. Culturally appropriate food recipes will be standardized and delivered with the help of dietician (co-guide).

**Nutritional Education & counseling** (for mothers) – Two sessions of nutrition education and counseling will be conducted for the mothers/caregivers.

- 1^st^sessionwill be conducted when the infants will be 6-8 months old.
- 2^nd^ session will be conducted when the infants will be 9-11 months old.

Both the sessions will be centered on feeding of infants, maintaining hygiene while cooking and eating and sanitation. Each session will last 30-45 minutes and will be conducted for 20-30 participants. Talks, group discussion and demonstration will be used to impart knowledge and skills of mothers related to infant and child feeding.

The control group will continue to receive standard care through routine health education offered by ANMs and *anganwadi* workers.

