***b. Intervention for health workers***

**Module for Health workers –** The module will have three parts and will be delivered as:

- Part 1--- orientation and introduction
- Part 2 --- communication skills
- Part 3 --- home visit tasks and procedures

The ANMs will be trained as nutrition counselors. They will receive training at baseline and the session will be repeated after 2 months. After the training, the ANMs will conduct a fortnightly home visits to counsel and support mothers for infant feeding practices. Supervisory visits will be conducted by the resident every two months to assess their work.

A sensitization meeting with families, ANMs and AWWs responsible for child health will be conducted before the training of mothers and another meeting will be conducted after two months. ANMs/ AWWs will visit the mothers/care givers in their homes fortnightly/monthly. They will prepare an individualized plan of each mother-infant dyad for infant growth based upon the family’s acceptability of food and affordability. They will observe how mother is feeding the baby, hand hygiene practices. They will accordingly counsel them and improve the feeding practices. They will also resolve any problem mothers are facing while feeding the baby. They will also organize the monthly group meetings of the mothers. In these meetings mothers will get a chance to learn from the peers whose child are showing weight gain and will be motivated through positive deviance model[38].

1. ***Supervision of health workers***
   1. A module will be developed for tracking of undernourished child. The infants will be weighed every month in the *anganwadi* centers. The anthropometric data of the infants will be entered in an excel sheet in computer and z score will be calculated. A monthly work plan showing the nutritional status will be prepared for each child in the study area. This work plan will be given to all the ANMs and *anganwadi* workers in the area, so that they can focus on mother-infant dyads with low infant growth.
   2. About 10% of the counseling sessions by the health workers with the mother-infant dyads in the field will be directly observed and supervised by the junior resident in the study area, and accordingly feedback to the health workers and mothers will be given.

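### The t-test, the chi-square test and the sample size treat infants as independent, although infants share centres, health workers and mothers' groups and each arm is a single area

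*Protocol*

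**What the plan says.** - **Allocation (Protocol, Study design).** "The study and control area will be selected purposively". Burail is the study area; for the comparison, "The control area will be Maloya, another urbanized village in Chandigarh". Under Sampling Technique, dyads are drawn at random within each area from lists held by the anganwadi centres. That selects infants; it does not allocate them to arms.
- **Health workers (Study design).** "Burail has 7 auxiliary nurse midwives (ANMs) and 19 anganwadi workers and centers". On the control side, "Maloya has 3 ANMs, 1 ASHA", together with 26 anganwadi workers and centres.
- **Delivery (Intervention Phase).** For the mothers' education, "Each session will last 30-45 minutes and will be conducted for 20-30 participants". Under the intervention for health workers, "After the training, the ANMs will conduct a fortnightly home visits to counsel and support mothers for infant feeding practices". Monthly mothers' meetings are also planned. Control mothers receive routine education from their own ANMs and anganwadi workers.
- **Sample size.** The formula for two independent means is used with 1.28, 1.96, an SD of 0.65 kg and a difference of 0.25 kg. The result is given as 182: "This is the minimum sample size of infants to be included in the study per arm". It becomes 202 after 10% attrition. There is no ICC or design effect.
- **Statistical Analysis.** "T-test will be used to assess level of significance in difference between the means of the group". Chi-square is named for proportions, and effectiveness is a difference in differences in mean change in weight. Clustering is not mentioned anywhere in the protocol.

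**The concern.** Infants who attend the same centre, are counselled by the same ANM or whose mothers sit in the same group are likely to resemble each other in feeding and growth. The protocol's own literature table makes this plausible: in a comparable counselling trial only 58% of trained health visitors performed adequately, so workers differ. A t-test on individual infants counts each as a full piece of independent information. If the ICC is positive, its standard error is too small, its p-value is too small, and the nominal 5% is exceeded.

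A second problem sits on top of this. Arm and area coincide. If growth trends differ between Burail and Maloya for reasons other than the intervention, the difference in differences will attribute that to the intervention. The protocol's aim is to assess effectiveness, and nothing in it limits the conclusion accordingly.

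**Working it through.** **Inputs.** From Sample size: SD 0.65 kg in both arms, difference 0.25 kg, multipliers 1.28 and 1.96, 182 per arm. From Study design: 19 and 26 centres, 7 and 3 ANMs. The ICC is not in the documents; 0.01, 0.02 and 0.05 are assumptions. Infants are assumed to be spread evenly over centres or ANMs.

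**1. The plan's own figure.** (1.28 + 1.96)² × (0.65² + 0.65²) / 0.25² = 10.4976 × 0.845 / 0.0625 = 141.9, so 142 per arm, not 182. The attrition step is consistent (182 / 0.9 = 202.2).

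**2. If infants were independent, with 182 per arm.** SE = 0.65 × √(2/182) = 0.0681 kg. Power for 0.25 kg = Φ(0.25/0.0681 − 1.96) = 95.6%.

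**3. With clustering.** Design effect in each arm: DE = 1 + (m − 1) × ICC, with m infants per cluster; the two arms are averaged. True type I error of the unadjusted test = 2 × [1 − Φ(1.96/√DE)]. Power with the correct standard error = Φ(0.25/(0.0681 × √DE) − 1.96).

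*Centre level:* m = 182/19 = 9.6 and 182/26 = 7.0.

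| ICC (assumed) | Mean DE | SE ratio | Type I error | Power |
|---|---|---|---|---|
| 0.01 | 1.07 | 1.04 | 5.8% | 94% |
| 0.02 | 1.15 | 1.07 | 6.7% | 93% |
| 0.05 | 1.36 | 1.17 | 9.3% | 88% |

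*ANM level, clustering in both arms:* m = 182/7 = 26 and 182/3 = 60.7.

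| ICC (assumed) | Mean DE | SE ratio | Type I error | Power |
|---|---|---|---|---|
| 0.01 | 1.42 | 1.19 | 10% | 87% |
| 0.02 | 1.85 | 1.36 | 15% | 77% |
| 0.05 | 3.12 | 1.77 | 27% | 55% |

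*ANM level, clustering in the intervention arm only* (DE = 1 in the control arm): mean DE is 1.125 at ICC 0.01 and 1.625 at 0.05. Type I error is 6.5-12.4% and power 93-82%.

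**4. Infants needed for 90% power, number of clusters fixed.** Solve 0.65² × [2(1 − ICC)/n + ICC/k₁ + ICC/k₀] = (0.25/3.24)² for n.
- Centres (k = 19 and 26): about 151 per arm at ICC 0.01, 160 at 0.02 and 200 at 0.05.
- ANMs (k = 7 and 3): about 213 at 0.01 and 430 at 0.02. Above an ICC of about 0.03 no number of infants is enough.

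**5. Area level.** With one area per arm, the degrees of freedom for between-area variance are 2 × (1 − 1) = 0. The variance cannot be estimated, whatever the model or the number of infants.

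**The case against.** Five arguments can be made for the plan.

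- *The protocol describes delivery at the level of the mother-infant dyad.* The same section sets up group sessions, and the next has one ANM visiting many dyads. Individual counselling by a shared worker is still clustered. This does not help.
- *Difference in differences deals with area.* In part. It removes fixed differences between Burail and Maloya. It does not remove different trends, and it does not correct the standard error.
- *A statistical analysis plan may specify a cluster model.* Possibly, and the protocol does not say how the standard error of the difference in differences is to be obtained. But it positively names the t-test and fixes a sample size without a design effect. These are stated choices, not details left for later.
- *The size is assumed.* This stands. No ICC is documented, and at centre level the harm is moderate: power remains above the 80% stated in the protocol.
- *The ANM figures lean on the control arm.* This also stands. The 61 infants per control ANM drive the upper end, yet those ANMs give only routine education. If ANM clustering arises only under the intervention, type I error peaks at about 12%, not 27%.

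A reader might also infer that 182 already contains a design effect, since 182/142 = 1.28. The documents do not support that: no such factor is mentioned, and 182 is presented as the direct result of a formula whose inputs give 142.

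**Conclusion.** The point holds. The stated tests and sample size ignore clustering that the protocol itself creates, and any positive ICC makes the standard errors and p-values too small. On an assumed ICC of 0.01-0.05, an even spread of infants and 182 per arm, type I error is about 6-9% at centre level (power 94-88%). It could reach about 10-27% if clustering acts at ANM level in both arms. The direction is firm; the size is not. The power figures also inherit the protocol's SD of 0.65 kg.

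Two stronger readings should be resisted.

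- The 27% is not the expected error rate. It needs the highest assumed ICC, at ANM level, in both arms.
- An error rate for area-level clustering can be written down: an ICC of 0.01 gives DE = 1 + 181 × 0.01 = 2.81 and about 24%. It is illustrative only. Area is completely confounded with arm, the areas were chosen purposively, and after differencing only area-specific trends matter, for which no ICC is known. This is a limit on interpretation, not a calculable error rate.

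**What to change.** 1. **Data.** Record anganwadi centre and ANM for every infant. Centre is available from the lists used for sampling.
2. **Primary analysis.** Test the difference between arms in mean change in weight for age with a linear mixed model, or GEE with a small-sample correction, clustered on centre (19 + 26 = 45).
3. **Secondary proportions.** Use the logistic equivalent in place of chi-square.
4. **Sensitivity analysis.** Repeat with ANM as the cluster, and say that 7 versus 3 clusters make it weak. If ANM effects dominate, the centre-level analysis may not fully hold 5%.
5. **Sample size section.** Correct the base to 142, then state the achieved power over a declared ICC range. Do not describe 182 as including a design effect. At 182 per arm the centre-level power stays at 88% or more over the assumed range; at ANM level it may not, so the text should not promise that the number is sufficient.
6. **Conclusion.** State that inference is conditional on these two areas and cannot separate the intervention from area-specific trends. Only more areas per arm would change that.

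The cost is one or two extra variables, revised analysis wording, slightly wider intervals, lower stated power and a more modest conclusion.
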